### Study setting

All three cardiac catheterization laboratories in the province of Alberta, Canada (total population 3.1 million people) are participating in this trial.

### Study participants

Eligible patients (and their primary care physicians) will be identified by the research assistants at the time of their cardiac catheterization and approached for written informed consent to participate in the study. Specific criteria for inclusion and exclusion include the following:

#### Inclusion criteria

Alberta residents older than age 18 who undergo a cardiac catheterization and are diagnosed with CAD on the basis of coronary angiography, demonstrating a stenosis in at least one coronary vessel of ≥ 50%[82].

#### Exclusion criteria

Patients will be excluded if: (1) they have not had a fasting lipid panel done in the six weeks prior to their cardiac catheterization; (2) they are already on a statin at maximal dose; (3) they are on a statin/lipid-lowering drug and the LDL cholesterol level is ≤ 2.5 mmol/l; (4) they are not on a statin but their fasting LDL is ≤ 1.8 mmol/L; (5) they do not have CAD proven on catheterization; (6) they are undergoing catheterization in the setting of an acute coronary syndrome or cardiogenic shock; (7) they die during the catheterization or require emergency bypass surgery; (8) the catheterization is being done as part of a research protocol; (9) they do not have an identifiable primary care physician; (10) they have contraindications to statin use (history of cirrhosis or inflammatory muscle disease, serum creatinine ≥ 200 umol/L, women of child-bearing age, or prior allergy to statins); and/or (11) they are already enrolled in ESP-CAD.

### Allocation to experimental arms

Randomization will take place 1:1:1 at the level of the practice (either individual physician for solo practitioners or clinic for those physicians who practice in a group setting) following the completion of the patient's coronary angiogram using a 'real-time' central randomization system with allocation concealment embedded in the APPROACH software. After a practice's first patient is randomized, all subsequent patients from that practice will be assigned to whatever treatment arm the first patient was randomized to.

While this is a form of cluster randomization, we anticipate the design effect to be negligible since the majority of physicians will contribute no more than one or two study patients, and thus all sample size and analytic considerations use the patient as the unit of analysis and the unit of causal inference.

### Outcome measures

We decided to focus on only those secondary prevention maneuvers that have strong evidence of survival benefits and are readily measurable from patient self-report and/or examination of pharmacy records. We decided not to examine factors (such as blood pressure control or LDL cholesterol levels) that would require in-person patient assessments, as this would substantially increase the complexity and expense of this study. If the interventions tested in this study are effective, then subsequent studies will extend the interventions (and their assessment) to address other cardiovascular risk factors such as control of blood pressure.

Although we mention five secondary prevention maneuvers in the local opinion leader and unsigned evidence statements (see Additional Files 1 and 2), we chose to emphasize statin prescribing in the statements (and as our primary outcome measure) because we felt the evidence for using statins in all patients with CAD (regardless of baseline cholesterol level) is more robust than the evidence for the use of ACE inhibitors or beta-blockers in all patients. Although the evidence in support of antiplatelet agents also is robust, we chose not to make this the primary outcome because of the likelihood that ASA prescribing may be close to maximal already (see Table 2).

#### Primary outcome

The primary outcome measure is a composite measure representing improvement in statin-related secondary prevention consisting of: 1) provision of a statin sample, or 2) provision of a statin prescription, or 3) increasing the dosage of a statin within the first six months post-angiogram. As this is a composite end-point, only the first event attained in the cluster will be counted for analysis, although all events will be recorded in the database.

Six months was chosen for the primary and secondary outcomes because the average number of physician visits in our audit of trial-eligible patients attending the University of Alberta cardiac catheterization laboratory in the 2003 year was 1.8 visits in six months. As we are assessing the impact of the Local Opinion Leader Statement and Unsigned Evidence Statement on physician practice patterns, for the purposes of this study we are interested solely in evaluating attempted practice change. In other words, if a patient is provided with a statin sample or a statin prescription, or the dosage is increased by any of the patient's physicians, it would still count as a positive outcome for the main study analysis, even if the patient cannot tolerate the medication and discontinues it or is noncompliant during follow-up. We recognize that patient (and physician) long-term compliance with preventive therapies is important, and will collect data on persistence rates with secondary prevention maneuvers over the six months of the study. We anticipate that this data will serve as pilot data for a planned future study on interventions to improve provider/patient persistence rates.

We will examine the primary outcome rates in all three treatment arms as follows: the primary comparison will be between those patients randomized to the Local Opinion Leader Statement versus usual care, and the secondary comparisons will be (a) between those patients randomized to the Unsigned Evidence Statement versus usual care, and (b) between those patients randomized to the Local Opinion Leader Statements versus Unsigned Evidence Statements.

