***Audits in patients discharged after acute myocardial infarction or coronary artery bypass surgery:***							
USA (39)	201 752	NR	30%	34%	83%	NR	NR
USA (37)	1710	12%	NR	44%	53%	NR	NR
USA (38)	622	37%	NR	23%	46%	25%	15%
USA (45)	190 015	NR	31%	NR	NR	NR	NR
USA (47)	25 000	NR	NR	NR	81%	NR	NR
Europe (40)	3379	58%	43%	66%	84%	21%	41%
Ontario(48)	9667	40%	65%	68%	NR	NR	NR
Quebec(48)	4790	43%	57%	68%	NR	NR	NR
British Columbia(48)	2570	42%	58%	61%	NR	NR	NR
Nova Scotia(48)	761	36%	58%	83%	NR	NR	NR
Alberta (APPROACH patients)**	5104	34%	39%	61%	81%	NR	NR

Note that while the general practice audits represent cross-sectional data at varying times after the diagnosis of CAD, the audits in patients discharged after acute MI generally represent prescribing data between 90 days and 120 days after MI.

* Target cholesterol defined as LDL cholesterol ≤ 2.6 mmol/L or total cholesterol ≤ 5.0 mmol/L.

** Medications in use at the time of the cardiac catheterization (no data available on prescriptions in follow-up). [[name], personal communication, August 2003]

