### Sample size

In a survey of 22 members of the divisions of cardiology and general internal medicine at the University of Alberta, we determined that the "minimal" clinically important difference for this particular intervention to be considered useful was a 15% absolute improvement over and above usual care. After six months, we estimate that no more than 20% of control patients will have attained our composite primary outcome, given that patients who are already on a statin and have optimal LDL cholesterol levels will be excluded from this study at baseline. We calculated our sample size to detect a 15% absolute increase in the primary outcome, set the α error rate at 0.05 (2-sided), and the β error at 0.20 (power 80%) – this yielded a sample size of 138 patients per study arm. Allowing for losses during follow-up, the ability to examine each of the conditions separately, and the possibility of a very small design effect associated with patient clustering, the total sample size has been adjusted upwards to 160 patients per arm (480 in total).

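### The primary composite, as written, scores an unchanged statin renewal as improvement in patients already on a statin at entry; success should be defined by baseline statin status

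*Protocol article*

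**What the plan says.** All references are to the protocol article.

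- **Primary outcome, definition.** The composite is presented as improvement in statin-related prevention and consists of "1) provision of a statin sample, or 2) provision of a statin prescription, or 3) increasing the dosage of a statin" in the first six months after the angiogram.
- **Primary outcome, scoring rule.** The rule is restated in the same section: it is a positive outcome "if a patient is provided with a statin sample or a statin prescription, or the dosage is increased by any of the patient's physicians", even if the drug is later stopped. Neither statement limits the sample or prescription to patients not on a statin at entry.
- **Primary outcome, purpose.** For this study, "we are interested solely in evaluating attempted practice change".
- **Exclusion criteria.** Statin users are excluded if "they are already on a statin at maximal dose" or if "they are on a statin/lipid-lowering drug and the LDL cholesterol level is ≤ 2.5 mmol/l". Users on a lower dose with LDL above 2.5 mmol/L remain eligible.
- **Sample size.** At six months, "we estimate that no more than 20% of control patients will have attained our composite primary outcome". The reason given is that statin users with optimal LDL are excluded. The target is a 15-point absolute increase, with 138 patients per arm raised to 160.
- **Study procedures and data collection.** Baseline medication use is recorded. Outcomes come from patient self-report at three and six months, cross-referenced to pharmacy records.

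**The concern.** The trial enrols two kinds of patient: those not on a statin, and those on a statin that is neither at maximal dose nor achieving the LDL threshold. For the first group, any sample or prescription is a change in care. For the second, a repeat prescription at the same dose is ordinary continuation, yet it meets component 2 as worded. The dose-increase component shows that baseline users were expected, but it does not restrict what components 1 and 2 count for them.

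Two things are at stake. The first is meaning: an endpoint that credits unchanged renewals does not measure improvement or attempted practice change. The second is dilution: renewals would occur in all three arms, which raises the control rate and compresses the absolute difference that the trial was sized to detect. Pharmacy records log renewals as readily as new starts, so whoever scores the outcome needs a written rule to separate them.

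**Working it through.** **Step 1. Reproduce the plan's figure.** Inputs from Sample size: 20% versus 35%, two-sided α = 0.05, power 80%. Two-proportion formula with pooled variance under the null and no continuity correction, p̄ = 0.275:

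n = [1.96·√(2·0.275·0.725) + 0.842·√(0.20·0.80 + 0.35·0.65)]² / 0.15² = 138 per arm.

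This matches the stated 138. The same formula gives 80.0% power at 138 per arm and 85.5% at 160. The sample size arithmetic is correct.

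**Step 2. Model the literal rule.** Let

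- s = share of enrolled patients on a statin at baseline;
- r = probability that a baseline user who does not otherwise improve receives a renewal within six months.

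Assume that genuine improvement is 20% versus 35% in users and non-users alike, and that r is the same in every arm. Then

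- control rate = 0.20 + 0.80·s·r;
- intervention rate = 0.35 + 0.65·s·r;
- difference = 0.15 − 0.15·s·r = 0.15 × (1 − s·r).

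Whenever s and r both exceed zero, the control rate is above 20% and the difference is below 15 points.

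**Step 3. Put in a range.** The protocol gives neither s nor r. For s, I take 0.10 to 0.34. The upper value is the Alberta registry entry in Table 2, whose footnote describes it as "Medications in use at the time of the cardiac catheterization"; it is not the trial-eligible subset and serves only as a point in the range. For r, I take 0.5 and 0.9, both assumptions.

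| s | r | Control | Intervention | Difference | Power at 160 per arm | n per arm for 80% power |
|---|---|---|---|---|---|---|
| 0 | – | 20.0% | 35.0% | 15.0 points | 85.5% | 138 |
| 0.10 | 0.5 | 24.0% | 38.3% | 14.2 points | 78.9% | 165 |
| 0.10 | 0.9 | 27.2% | 40.9% | 13.7 points | 73.3% | 188 |
| 0.20 | 0.5 | 28.0% | 41.5% | 13.5 points | 72.0% | 195 |
| 0.20 | 0.9 | 34.4% | 46.7% | 12.3 points | 61.1% | 249 |
| 0.34 | 0.5 | 33.6% | 46.1% | 12.4 points | 62.5% | 242 |
| 0.34 | 0.9 | 44.5% | 54.9% | 10.4 points | 46.1% | 361 |

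Worked line for s = 0.34, r = 0.9: s·r = 0.306; control 0.20 + 0.80·0.306 = 0.445; intervention 0.35 + 0.65·0.306 = 0.549; difference 0.15·0.694 = 0.104.

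**Step 4. Compare with the 20% ceiling.** Under the literal rule, if s·r exceeds 0.20, the control rate exceeds 20% even with no genuine improvement in controls. The justification in Sample size rests on excluding users with optimal LDL; it does not address the users who stay in.

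**The case against.** The best reply is that the text already points away from counting renewals. The outcome is framed as improvement and attempted practice change, and a same-dose refill is neither. If every prescription counted, the dose-increase component would be nearly redundant. The 20% ceiling is hard to hold if renewals count and natural if they do not, so it is evidence of what the authors meant. The restated scoring rule is chiefly about tolerability and later discontinuation, which suits a newly given drug. Detailed coding of refills may also sit in forms or a plan that are not shown.

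Most of this stands as evidence of intent. It does not remove the problem: the article states a rule, twice, and followed as stated it credits renewals. That is more than an omitted detail.

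Three further points for the defence deserve weight.

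- **Magnitude.** A reader might infer that almost every baseline user becomes a success and that the planned power is gone. The documents do not support that. They give no user share among eligible patients and no renewal probability. The Background section cites one-year statin persistence of 43% to 75%, so r = 0.9 may be high. At s = 0.10 and r = 0.5, power is still 79%, close to the planned 80%.
- **Interim look.** The planned look at 80 patients per arm checks event rates and could raise the sample size. It would soften the power loss, but it could not make a renewal measure improvement.
- **Blinded follow-up.** With blinded outcome assessment, miscounted renewals would mainly dilute the effect, not favour an arm.

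**Conclusion.** The concern holds as a defect in the wording of the primary endpoint. Eligibility admits baseline statin users, and components 1 and 2 are not limited to new starts, so the literal rule conflicts with the endpoint's stated purpose and with the basis of the control rate. New starts or intensification were probably intended, but the article nowhere says so.

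The direction of the effect is certain under the literal reading, given the equal-renewal assumption: a higher control rate and a smaller difference. Its size is not. Power at 160 per arm runs from about 79% to 46% over the assumed range, against 85.5% if renewals are not counted. These figures are illustrative and apply only if renewals are in fact scored.

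A reader might also take the statement that "only the first event attained in the cluster will be counted for analysis" to mean one event per practice, contradicting the patient as unit of analysis. The documents do not support that reading: the sentence opens by referring to the composite, so the word most naturally means the group of component events, and the allocation and analysis sections fix the patient as the unit. Because cluster elsewhere in the article refers to the practice-level randomization, it is a minor wording point and adds nothing to the main one.

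**What to change.** Define success by baseline statin status:

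- **Not on a statin at baseline:** a first statin sample or prescription within six months counts.
- **On a statin at baseline:** only a dose increase, or a switch that intensifies therapy according to a list fixed in advance, counts. A renewal or sample of the same regimen does not.

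Confirm that the 20% control rate refers to this definition. If it does, 138 per arm for 80% power and 85.5% at 160 per arm stand unchanged.

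As a separate clarification, replace the phrase about the cluster with *first component event in each patient*.

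The cost is a few sentences and a comparison of baseline drug and dose with the follow-up record. Baseline medication use and pharmacy records are already collected. The drawback is the extra work of that comparison and of agreeing the list of intensifying switches before outcomes are scored.

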#### Secondary outcomes

Secondary outcomes will include the provision of other proven efficacious medications for CAD by six months, including ACE inhibitors, beta-blockers, and antiplatelet agents; these medications will be considered independently as individual end-points in eligible patients. Moreover, we will examine changes in the provision of other lipid-lowering medications (fibrates, niacin, and/or resins), as well as self-reported smoking rates, receipt of smoking cessation advice, provision of nicotine replacement products, or buproprion in trial patients within six months of their angiogram. We also will record whether study participants have a fasting lipid profile done in the six months post-angiogram and, for the subgroup of patients who have a fasting lipid profile done during follow-up (i.e., done for clinical reasons by their attending physicians, not mandated by the trial protocol), we will examine the proportion of patients achieving target LDLs compared to baseline. Finally, we also will analyze clinical events (MI, stroke, admissions for CAD, total hospitalizations, and mortality) in the three arms of this study, although the study is not powered to find any differences in these end-points over such a short timeframe.

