#### The potential role of point-of-care reminders and opinion leaders in closing care gaps

In looking for a simple, effective and evidence-based means to improve the quality of care for patients with CAD, we have isolated 2 key elements – point-of-care reminders and educational materials endorsed by local opinion leaders that form the basis of the quality improvement intervention to be tested in this trial[58].

The interface between hospital-based specialists and community-based primary care physicians is frequently imperfect, and this system barrier likely affects the quality of care for patients with CAD. Reminder systems, particularly those which are clear, patient-specific, and delivered at the point of care, can improve communication and the delivery of health services in numerous settings, although the effects are often modest[59]. A recent systematic review, however, concluded that the effects of point-of-care reminders sent by specialists to primary care physicians had been inadequately evaluated[59].

This is particularly significant because surveys of primary care physicians consistently confirm the importance of colleagues and local consultants on patterns of practice[60,61]. In fact, several recent studies suggest that the mere provision of evidence without specialist input, even with a point-of-care reminder at the time patients are being seen, may not be enough to change practice in CAD. For example, although the mailing of patient-specific reminders (from the local health authority) about secondary prevention therapies to the primary care physicians of MI survivors in England led to higher rates of cholesterol measurement and recording of cardiac risk factors in these patients, there was no appreciable difference in statin prescribing rates[62]. Similarly, faxing care management summary sheets (listing diagnoses, medications, pertinent laboratory data, and guideline recommendations for each patient) to the primary care physicians of patients with diabetes and dyslipidemia did not significantly impact statin prescription rates[63]. Finally, four trials testing the effects of computerized decision support systems that prompted primary care practitioners with reminders and management guidelines (which were not explicitly endorsed by local opinion leaders) when they were seeing patients with CAD reported negligible improvements in prescribing of statins or other proven efficacious therapies compared to controls. [64-67]

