### Details of the intervention

The Local Opinion Leader Statement is a one-page summary of evidence-based secondary prevention strategies and treatment recommendations for patients with CAD, and contains the signatures of all five CAD local opinion leaders identified by our survey of primary care practitioners (see Additional file 1). The emphasis is on statin prescribing – as a result, statins are recommended first (listing only those statins which have been proven efficacious in large trials), and the letter explicitly mentions their starting and target doses, usual titration schedules, and monitoring parameters. For each of the other secondary prevention therapies (ACE inhibitors, antiplatelet agents, beta-blockers), we list only the drug class in the Opinion Leader Statement without explicit statements about dosing, titration, or monitoring parameters.

The Local Opinion Leader Statement will be imprinted with the name of the patient and addressed directly to the primary care physician. The statement will be faxed to the physician following the completion of the patient's coronary angiogram along with objective evidence of the patient's CAD (the Alberta Provincial Project for Outcome Assessment in Coronary Heart Disease [APPROACH] HeartView Diagram which documents the extent of the patient's coronary atherosclerosis)[81]. All of the faxes (APPROACH HeartView diagrams and the one page statement) will be generated and sent automatically using a software program that has been developed for this trial and embedded in the APPROACH software. It is intended that the statement and the HeartView Diagram will become part of the patient's medical record and will serve as a reminder for action at the next patient visit.

The Unsigned Evidence Statement, identical to the Local Opinion Leader Statement in content but without the local opinion leader signatures (see Additional file 2), will be faxed to the primary care physician, along with the APPROACH HeartView Diagram, in the same manner as described above.

Physicians of control patients (usual care) will receive a fax containing only the APPROACH Heartview Diagram. This will ensure that all physicians and patients receive the same number of study related materials and encounters, with the only difference being the content of the fax.

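### LDL target attainment is examined only in patients whose physicians ordered a lipid test after randomisation, so this secondary result is at risk of selection bias of unknown direction

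*Protocol article*

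**What the plan says.** In the protocol article, Secondary outcomes commits to three things about lipids.

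- Testing is itself an outcome: "We also will record whether study participants have a fasting lipid profile done in the six months post-angiogram".
- LDL attainment is restricted to tested patients: "for the subgroup of patients who have a fasting lipid profile done during follow-up". The tests are described as "done for clinical reasons by their attending physicians, not mandated by the trial protocol".
- The quantity of interest is given as "we will examine the proportion of patients achieving target LDLs compared to baseline".

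Other analyses states that secondary outcomes will be handled with methods similar to those for the primary outcome. Those methods are chi-square comparisons between arms under intention to treat (Statistical analyses).

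Three other places bear on who gets tested.

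- On statins, Details of the intervention says that "the letter explicitly mentions their starting and target doses, usual titration schedules, and monitoring parameters". By contrast, "Physicians of control patients (usual care) will receive a fax containing only the APPROACH Heartview Diagram".
- The section on point-of-care reminders describes a mailed, patient-specific reminder programme in England that "led to higher rates of cholesterol measurement and recording of cardiac risk factors in these patients", without a material change in statin prescribing.
- Study procedures and data collection says that primary care physicians cannot be blinded.

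**The concern.** Having a lipid profile is an event after randomisation, and it is decided by the physicians whose behaviour the trial is trying to change. If a statement fax prompts tests that would not otherwise have been done, the tested patients in that arm are a different selection from the tested patients under usual care. The proportion at target among the tested can then differ between arms when LDL control does not, or overstate or understate a real difference. The restriction also departs from the intention-to-treat principle stated for the trial's analyses.

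Reading the outcome as a change from baseline within each arm does not avoid the difficulty. Patients on lipid-lowering treatment are excluded if their LDL is 2.5 mmol/L or lower (Exclusion criteria), so treated patients are selected for a high value. Some would fall below the cut-off on re-measurement with no change in care.

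At stake is what the trial may say about LDL control, its only outcome on lipid levels.

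**Working it through.** **The plan's own figure.** The article gives no figure for the LDL outcome. Its 138 per arm concerns the primary outcome (20% vs 35%, two-sided 0.05, power 80%). With pooled variance, [1.960 × √(2 × 0.275 × 0.725) + 0.842 × √(0.20 × 0.80 + 0.35 × 0.65)]² / 0.15² = 137.9, so 138 is reproduced. It does not bear on this point.

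All inputs in the two illustrations below are assumptions, except the 20% and 35% statin-change rates, which are borrowed from Sample size.

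**Illustration 1: no true difference, extra tests drawn from patients less often at target.** Assume 30% at target in every arm, and 40% of controls tested, of whom 45% are at target.

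- Untested controls at target: (0.30 - 0.40 × 0.45) / 0.60 = 20%.
- Intervention arm with 60% tested, the extra 20% coming from that remainder: (0.18 + 0.20 × 0.20) / 0.60 = 36.7%, against 45%. False difference: -8.3 points.
- With 50% tested: (0.18 + 0.10 × 0.20) / 0.50 = 40%, against 45%. False difference: -5 points.

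**Illustration 2: testing depends on statin change.** Let s be the share with a statin change, a and b the chance of a test with and without a change, and t1 and t0 the chance of being at target with and without a change. Then

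proportion at target among the tested = [s·a·t1 + (1 - s)·b·t0] / [s·a + (1 - s)·b].

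Take t1 = 0.50, t0 = 0.10 and s = 0.20 in both arms. True attainment is 0.20 × 0.50 + 0.80 × 0.10 = 18% in each arm.

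| Control (a, b) | Intervention (a, b) | Tested-only, control | Tested-only, intervention | False difference |
|---|---|---|---|---|
| 0.7, 0.4 | 0.7, 0.6 | 0.102/0.46 = 22.2% | 0.118/0.62 = 19.0% | -3.1 |
| 0.8, 0.3 | 0.8, 0.5 | 0.104/0.40 = 26.0% | 0.120/0.56 = 21.4% | -4.6 |
| 0.6, 0.4 | 0.9, 0.4 | 0.092/0.44 = 20.9% | 0.122/0.50 = 24.4% | +3.5 |
| 0.5, 0.5 | 0.7, 0.7 | 0.090/0.50 = 18.0% | 0.126/0.70 = 18.0% | 0 |

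The sign depends on whom the fax causes to be tested. The bias vanishes when extra testing is unrelated to statin change and hence to LDL.

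**With a real effect.** Let s be 20% vs 35%, with a and b the same in both arms. The true difference is 24% - 18% = 6.0 points. Tested-only, it appears as 6.8 points (a = 0.7, b = 0.5) or 7.6 points (a = 0.9, b = 0.3).

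**All randomised patients, untested counted as not documented.** Under the same nulls, illustration 1 gives 0.40 × 0.45 = 18% vs 0.60 × 0.367 = 22%. The last row of illustration 2 gives 9.0% vs 12.6%. This is a valid randomised contrast, but of testing and control together.

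**Change from baseline.** Secondary outcomes does not state the target. If it lies near 2.5 mmol/L, treated patients start at or near 0% attainment because of the entry criterion, and regression to the mean can only raise that figure.

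**The case against.** The strongest reply has five parts.

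- **Differential testing is not shown.** The cited reminder study had a different sender and setting. The monitoring parameters might be safety tests rather than lipid panels, and the statement itself is not at hand. This stands. A reader might infer that the intervention does change the tested group and that the comparison is therefore biased, but the documents support only a credible risk, of either sign or none.
- **No between-arm LDL test is spelled out.** The sentence speaks of comparison with baseline, and a test between arms is inferred from the general remark under Other analyses. This stands too, so it would be too strong to say that the randomised comparison is lost. The before-after reading, however, has its own weakness.
- **Regression to the mean affects all arms alike.** The entry cut-offs are common to the arms, so it undermines a within-arm change and does not by itself bias a contrast between arms.
- **The size is assumed, and chance would swamp it.** In the worst case above, with about 64 and 96 tested out of 160 per arm, the 8.3-point gap has a standard error of √(0.45 × 0.55/64 + 0.367 × 0.633/96) = 7.9 points, ignoring clustering (z about 1.05). It would usually not reach significance, but the estimate would still mislead.
- **Matters are partly disclosed.** The article says that testing is not mandated and records it for everyone. That makes the fix easy, but does not make the tested-only proportion comparable between arms.

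A reader might also see a contradiction with Outcome measures, which says "We decided not to examine factors (such as blood pressure control or LDL cholesterol levels". The sentence goes on to limit this to factors needing in-person assessment, whereas lipid panels come from centralised laboratory data (Study procedures and data collection). The two places are compatible.

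**Conclusion.** The concern holds as a risk. The LDL denominator is fixed after randomisation by unblinded physicians, and the article's own account of the faxes and of earlier reminders makes a difference in testing plausible. With no true effect, the illustrations give false differences from -8.3 to +3.5 points, including zero. They rest on assumed testing and attainment rates, so they show possible size and not a forecast. The before-after reading is also unsafe, for treated patients, because of the LDL entry criterion.

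This concerns one secondary outcome. The primary statin outcome does not depend on lipid testing and is unaffected. The change is still worth making, because it alters what the trial may conclude about LDL control.

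**What to change.** - Label the tested-only LDL result exploratory and descriptive, without p-values, whether shown by arm or against baseline.
- Show the lipid-testing rate by arm beside it.
- Make any between-arm inference in all randomised patients, on LDL documented at target within six months, with untested patients counted as not documented. State that this endpoint combines testing and control and is not evidence of LDL control alone.
- Add sensitivity analyses for untested patients, for example imputation from baseline LDL and statin change, or a range of assumed values for the untested in each arm.

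No new data are needed: testing, laboratory results, baseline cholesterol and statin changes are already to be collected. The cost is a little more analysis and a more cautious conclusion about LDL.
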